## Abstract

**Introduction:**

Bacterial infection represents a serious risk in neonates and critically ill paediatric patients. Current clinical practice is characterized by frequent antibiotic treatment despite low incidence of true infection. However, some patients escape early diagnosis and progress to septic shock. Many new markers, including cytokines, have been suggested to improve decision making, but the clinical efficacy of these techniques remains uncertain. Therefore, we will test the clinical efficacy of a previously validated diagnostic strategy to reduce antibiotic usage and nosocomial infection related morbidity.

**Methods:**

All patients admitted to the multidisciplinary neonatal and paediatric intensive care unit of a university children's hospital will be included. Patients will be allocated either to routine sepsis work up or to the intervention strategy with additional cytokine measurements. Physicians will be requested to estimate the pre-test probability of sepsis and pneumonia at initial suspicion. In the treatment arm, physicians will receive raw cytokine results, the likelihood ratio and the updated post-test probability. A high post-test probability will suggest that immediate initiation of antibiotic treatment is appropriate, whereas a low post-test probability will be supportive of watchful waiting or discontinuing prophylactic empirical therapy. Physicians may overrule the suggestions resulting from the post-test probability.

**Conclusion:**

This trial will ascertain the clinical efficacy of introducing new diagnostic strategies consisting of pre-test probability estimate, novel laboratory markers, and computer-generated post-test probability in infectious disease work up in critically ill newborns and children.

## Introduction

Bacterial infection is an important cause of mortality and morbidity in newborns and critically ill paediatric patients [1,2]. The high risks associated with untreated infection and the lack of accurate clinical or laboratory prediction methods result in a low threshold for initiating empirical antibiotic therapy. In neonatal and paediatric intensive care, antibiotic therapy is used in as many as 80% of patients, with an average of about 50% [3]. Only a minority of treated patients suffer from true infection. The majority receive antibiotics for 48–72 hours because clinical signs suggest possible infection and laboratory parameters are unable to rule out infection. In otherwise healthy newborns, this practice causes prolonged separation from the mother and increased the costs of care [4,5]. The high prevalence of unnecessary antibiotic therapy augments the risk for selecting resistant bacterial strains. Despite liberal antibiotic prescription, in some patients sepsis is not diagnosed until they have progressed to serious conditions such as septic shock.

Several groups have suggested that measurement of cytokines may be done to facilitate early diagnosis [6-8]. We previously reported diagnostic test accuracy studies in which we derived a prediction model based on the measurement of plasma levels of granulocyte colony-stimulating factor (G-CSF) and IL-8, and tracheal aspirate levels of G-CSF [9,10]. If plasma cytokine concentrations rise above pre-specified thresholds, then serious bacterial bloodstream infection is highly likely. Gram-negative sepsis is practically excluded if plasma levels remain low. Although plasma measurements assist in ruling out life-threatening sepsis, localized infections such as ventilator-associated pneumonia [11] cannot be diagnosed on the basis of blood derived cytokine concentrations. However, we previously showed tracheal aspirate levels of G-CSF to assist in diagnosing ventilator-associated pneumonia [10], which is the most frequent reason for prescribing antibiotics in our unit [3]. We recently conducted validation studies for plasma measurements of IL-8 and G-CSF and tracheal aspirate levels of G-CSF, employing a new laboratory method that allows simultaneous determination of parameters from 50 μl blood or tracheal aspirate. We refined the fluorescent bead-based immunoassay to reduce the assay turnaround time from 4.5 hours to 2 hours, rendering it suitable for routine clinical use.

To assess the clinical efficacy of the new diagnostic measures, we suggest that a randomized controlled trial be conducted comparing two management strategies. The control strategy will consist of routine management, with the exception that physicians are requested to provide a probability estimate for the presence of bacterial infection whenever a diagnostic work up (blood cultures or tracheal aspirate culture) is ordered. The intervention strategy will consist of cytokine measurement from the sample and provision of a result based post-test probability within a few hours after sample collection. The null hypothesis states that the management arms will not differ with respect to antibiotic utilization rate, measured as the number of days on systemic antibiotic treatment per 1000 days of hospitalization. The secondary null hypothesis states that the arms will not differ with respect to costs associated with hospital acquired septic shock.

## Methods

### Design

The study is a multicentre randomized controlled trial comparing a new diagnostic treatment strategy for diagnosing bacterial infection versus standard care in critically ill newborns and children. During a 16-week period in 2003 we conducted a pilot study, which tested the intervention and data collection procedures, and led to modifications to the study design. The pilot study is outlined in detail below. In brief, physicians provide pre-test probabilities whenever they order a diagnostic work up for sepsis or ventilator-associated pneumonia (microbiological cultures). This includes any prescription of antibiotics. In the intervention arm, physicians are provided with cytokine results and the updated post-test probability. In the control arm no information is given.

### Eligibility criteria for participants

All patients admitted to the interdisciplinary neonatal or paediatric intensive care unit (ICU) of the Children's Hospital of Zurich are eligible. Patients who are referred to other wards within 24 hours after admission will be excluded from data analysis, because in these patients the decision to stop antibiotic treatment is no longer the responsibility of participating intensivists.

### Setting

The participating university hospital is the tertiary referral centre for Eastern and Southern Switzerland, and serves a population of approximately 3 million. The Department of Neonatology and Pediatric Intensive Care at the University Children's Hospital of Zurich contributes patients from its two ICUs, named unit A and unit B. Both units have average occupancy of 8–10 beds. The two units admit between 900 and 1000 patients annually, with the number of hospitalization days amounting to 5500 each year. The patient population in unit A includes infants of extremely low birth weight referred from other hospitals, critically ill children and adolescent patients, trauma victims and high-risk surgical patients. Unit B predominantly cares for infants and children who have undergone cardiac surgery.

### Intervention and controls

#### Control strategy

For patients randomized to the control arm, if the physician orders microbial cultures then they are obliged to document their best estimate of the probability that the patient has sepsis or pneumonia on two logarithmic visual-analogue scales (range 0–100%). This documentation is mandatory and must be marked on the laboratory form (Fig. 1). In the control arm blood or tracheal aspirate specimens are not analyzed; thus, physicians do not receive any information beyond routinely available data. Under the control strategy antibiotic treatment is managed according to current recommendations (cessation of therapy after 48 hours provided that blood cultures remain negative).

#### Intervention strategy

If patients are randomized to the intervention arm, then physicians are also obliged to document their best estimate of the probability that the patient has sepsis or pneumonia, again on two logarithmic visual-analogue scales (range 0–100%). This documentation is again mandatory and must be marked on the laboratory form (Fig. 1). In the intervention arm, blood or tracheal aspirate specimens are analyzed and results are returned to the unit before 1 p.m. Physicians receive the raw cytokine values as well as the calculated likelihood ratio and the post-test probability (Fig. 2). This information is provided in addition to routinely available data. Provided that the available post-test probability indicates absence of infection, physicians are encouraged to stop antibiotic treatment. It is suggested that antimicrobial therapy be continued if the post-test probability indicates infection. It is important to note that the protocol provides only 'suggestions', and that the final decision regarding therapy is left to the discretion of the responsible clinician. This is similar to clinical routine, in which diagnostic results may suggest alterations to treatment decisions but they do not dictate treatment.

### Randomization

The units of randomization are calendar days. Randomization is generated through pre-specified assignment of 15 working days/month as intervention days. Physicians remain blinded to the allocation roster. Thirty minutes after the deadline for delivery of samples to the laboratory (10 a.m.), physicians are informed about the randomization status (control or intervention) of the day. In this way, physicians are able to adjust their decision making while they await test results if they so wish.

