### Measures of outcome

The primary outcome measure is the rate of systemic antibiotic use per 1000 days of hospitalization (see details under Sample size calculation and statistical considerations). Secondary outcome measures are as follows (for all episodes of hospital acquired infection with positive blood cultures for the first 7 days following initiation of antibiotics after adjusting for important possible patient confounders): number of days free from mechanical ventilation (an indicator of respiratory failure); number of days free from inotropic support (an indicator of circulatory failure); costs for specific expensive medications (e.g. fresh frozen plasma); and nurse allocation (an indicator of treatment intensity).

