### Sample size calculation and statistical considerations

At present, in the ICU antibiotic therapy is employed in 40% of patients, which represents a decline from our original survey conducted in 1998 (up to 80% of all patients) [3]. The expected reduction in antibiotic usage is 10–25%, with a clinically relevant reduction considered to be any reduction in excess of 10%. The minimum number of days of hospitalization in each arm required to detect a 10% reduction with a type I error under 5% and a power of 80% is 2300. The expected follow up rate is in excess of 90%. Because the unit of randomization is days and not individuals, an unknown intracluster (intraday) correlation coefficient must be considered. The standard χ^2 ^statistic, which assumes independence of individuals, may not be applicable. We may be forced to acknowledge the nested nature of the data (clustered randomized controlled trial) by using test statistics based on the generalized linear mixed model [12]. To safeguard against insufficient power we believe that the sample size must be increased to 25%, leading to a required accrual of 3000 hospitalization days per arm. Given the size of the participating units, this translates to a study duration of 24 months.

All analyses will be carried out on an intention-to-treat basis. This means that any antibiotic treatment course will be allocated according to the randomization status of the day on which the decision to withhold or to continue had to be made. This requires us to perform three subgroup analyses: antibiotic prescription prevalence according to the day's randomization status; antibiotic free days following the 4 days after any microbiological work up; and antibiotic free days during the week following any initiation of antibiotics.

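### Intervention days are drawn only from working days; if all other calendar days serve as control, day type is confounded with arm in the primary comparison

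*Protocol article*

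**What the plan says.** Under Randomization, the protocol article states "The units of randomization are calendar days" and then "Randomization is generated through pre-specified assignment of 15 working days/month as intervention days". It says of concealment "Physicians remain blinded to the allocation roster". Half an hour after the 10 a.m. sample deadline, "physicians are informed about the randomization status (control or intervention) of the day".

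Under Measures of outcome, "The primary outcome measure is the rate of systemic antibiotic use per 1000 days of hospitalization".

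Under Sample size calculation and statistical considerations, the current level is that "in the ICU antibiotic therapy is employed in 40% of patients", and the calculation ends with two equal arms, "leading to a required accrual of 3000 hospitalization days per arm". The intention-to-treat rule assigns each antibiotic course to the arm of its decision day. One of the three analyses listed there compares prescription prevalence by the day's randomization status.

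The article does not say whether weekends and holidays are control days or lie outside the comparison. It mentions adjustment for patient confounders only for the secondary outcomes. For the primary outcome it names neither a restriction to certain types of day nor an adjustment for type of day.

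**The concern.** The two sentences on the unit and the allocation do not fit together. If calendar days are randomized, each should have some chance of either arm. Here a weekend or holiday has probability 0 of being an intervention day, while a working day has a probability of about 0.7.

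If non-working days count as control, the control arm is a mixture of weekdays and weekends, and the intervention arm is weekdays only. The two kinds of day may well differ. The Setting section describes a cardiac surgery unit and a unit with high-risk surgical patients, so case mix, staffing and the threshold for a work-up could follow the working week. A difference of that kind would be read as an effect of the cytokine strategy, or would hide one. The mixed model that the article mentions deals with correlation within days, not with this imbalance. Adjusting for day type cannot supply the missing comparison, because no weekend intervention days exist.

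**Working it through.** **Inputs.** From the article: 15 intervention days a month; 5,500 hospitalization days a year; 24 months; 3,000 hospitalization days per arm; 40% baseline; 10% reduction; 5% type I error; 80% power. Assumed, because the article does not give it: 21 to 21.75 working days a month (the upper figure ignores holidays).

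**1. The plan's own figure.** Two proportions, 0.40 against 0.36, two-sided 5%, 80% power, independent days:
n = [1.960 × √(2 × 0.38 × 0.62) + 0.842 × √(0.40 × 0.60 + 0.36 × 0.64)]² / 0.04² ≈ 2,311 per arm.
This agrees with the stated 2,300, so the target effect is 4 percentage points.

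**2. Chance of intervention by type of day.** Working day: 15/21.75 = 0.69 to 15/21 = 0.71. Weekend or holiday: 0.

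**3. Make-up of the arms if all other calendar days are control.** Days per month = 365/12 = 30.42. Control days = 30.42 − 15 = 15.42, close to the 15 intervention days and in line with equal arms. Share of control days that are non-working:
- (30.42 − 21.75)/15.42 = 8.67/15.42 = 56%
- (30.42 − 21)/15.42 = 9.42/15.42 = 61%

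The corresponding share in the intervention arm is 0%.

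**4. Size of the shift (illustration only).** With no effect of the test, difference between arms = share × weekday–weekend gap in antibiotic prevalence.

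| Assumed gap | Shift between arms | Chance of P < 0.05 with no test effect |
|---|---|---|
| 2 points | 0.56 to 0.61 × 2 = 1.1–1.2 points | 14–16% |
| 5 points | 0.56 to 0.61 × 5 = 2.8–3.1 points | 61–68% |

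The last column takes 3,000 independent days per arm and a 40% rate in one arm.

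**5. What a restriction to working days leaves under the existing roster.** Average occupancy = 5,500/365 = 15.07.
- Intervention: 15 × 24 × 15.07 ≈ 5,425 hospitalization days.
- Control: (21 − 15) × 24 × 15.07 ≈ 2,170, to (21.75 − 15) × 24 × 15.07 ≈ 2,440.
- Equivalent equal-arm size, 2/(1/n₁ + 1/n₂): 2/(1/5,425 + 1/2,170) ≈ 3,100, to 2/(1/5,425 + 1/2,440) ≈ 3,370 per arm.

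Power for 40% against 36% is then about 90–92%, compared with 89% for 3,000 per arm, both with independent days.

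**6. Month-end days fixed by the quota.** With 15 intervention and 6 control days in random order, the expected number of days at the end of the month whose status is already determined is 15/(6 + 1) + 6/(15 + 1) = 2.14 + 0.38 ≈ 2.5.

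**The case against.** The strongest objection is that the article never says weekends and holidays are control. If only working days are in the trial, there is no weekend imbalance, and the full protocol may say so. This stands, and the point is therefore conditional. The near-equal split of 15 to 15.4 days favours the calendar-day reading, as does the stated unit. Accrual does not settle it: that reading gives about 5,425 and 5,575 hospitalization days in 24 months, and neither figure is the planned 3,000.

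A second objection is that the size of any weekday–weekend gap has no source in the article. It adds that courses of 48–72 hours, which the Introduction describes as usual, run across weekdays and weekends and would dampen a difference in daily prevalence. Both parts are fair. The shifts above are what-if figures, not estimates.

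A third objection concerns foreknowledge. The roster is hidden and status is disclosed only after the sample deadline. Those safeguards carry weight, so the predictability of the quota is secondary here.

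Three stronger readings are tempting, and the article does not support them:
- **A working-days-only trial would be underpowered because control falls short of 3,000.** It would not be. The larger intervention arm makes up for the shortfall (step 5), and unequal allocation is not a bias.
- **The fixed quota makes allocation largely guessable.** With 15 of 21 working days assigned, always guessing intervention is right 71% of the time. Counting past days raises this only to about 74%, so most of that figure is the allocation ratio.
- **Choosing when to order a work-up selects who enters the primary analysis.** The primary outcome is a rate over hospitalization days, not over work-ups. Work-up timing bears on the work-up-based analysis listed beside it.

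**Conclusion.** The concern holds in conditional form. As written, the allocation rule gives weekends and holidays no chance of intervention. If they are counted as control, 56–61% of control days have no counterpart in the intervention arm, and nothing stated for the primary outcome removes the imbalance. A gap of 2 to 5 points would put a shift of about 1 to 3 points into a contrast designed to detect 4. The direction and true size of the shift cannot be derived from the article.

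The conclusion rests on three assumptions: the inferred control status of non-working days, 21 to 21.75 working days a month, and even occupancy across the week. The precision figures treat days as independent and use all 5,500 hospitalization days a year. The exclusion of patients referred elsewhere within 24 hours would lower them by an amount the article does not give.

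**What to change.** State in the Randomization section how weekends and holidays are handled. Restrict the primary comparison of antibiotic days per 1,000 hospitalization days, numerator and denominator alike, to working days, the only days that could be assigned to either arm. Report weekend and holiday days descriptively and not as controls. The rule should also say where the days of a course that crosses a weekend are counted. Keep the stated primary outcome: a comparison based on work-ups would replace it and remove the basis of the sample size, which is in hospitalization days.

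This costs one analysis-set rule. The price is the loss of weekend days and an intervention-to-control ratio of about 2.2:1 to 2.5:1. The sample-size section should restate the arm sizes as roughly 5,400 and 2,170–2,440 hospitalization days in 24 months, and should check the clustering allowance against those sizes.

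If the roster can still be changed, randomize working days about 1:1, stratified by weekday and without a fixed monthly total. That also removes the roughly 2.5 working days a month whose status the quota and daily disclosure give away. At 21 working days a month it would yield about 10.5 × 24 × 15.07 ≈ 3,800 hospitalization days per arm in 24 months. The cost is a new roster in a trial described as ongoing, and fewer intervention days a month (about 10 to 11 instead of 15).

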### Data collection

Routine sepsis work up includes collection of blood cultures, other microbial specimens where appropriate, and measurements of white blood cell count, including differential and plasma levels of C-reactive protein. Routine surveillance for ventilator-associated pneumonia comprises microbiological examination of the tracheal aspirate, including cultures. As described above, physicians must provide two probability estimates, one for the presence of sepsis and one for pneumonia, whenever they order a sepsis or pneumonia work up. This ensures that clinicians state their estimate before knowledge of the test result. These estimates (pre-test probabilities) are integrated with cytokine concentrations derived from likelihood ratios for sepsis or pneumonia using Bayes' theorem. The algorithms for calculating post-test probabilities are presented in Table 1. A study nurse records clinical data for both groups on the day preceding collection of culture specimens and on the following 6 days (Fig. 3). We will collect data on mortality, but this will not be included as a study outcome because of low mortality rates and the intended study size. Further data are collected from the hospital's database. This database contains all physician's reports, patient baseline data, routine laboratory results, pharmacology data, costs per patient and day of specific medications (e.g. fresh frozen plasma), and staff allocation.

### Cytokine measurement

Blood samples are collected until 10 a.m. in EDTA-containing vacutainers. Immediately thereafter they are centrifuged at 3000 rpm for 10 min and plasma removed for cytokine analysis. Tracheal aspirate samples are obtained through the endotracheal tube using a sterile suction system (Medinorm AG, Quierschied, Germany). Samples are centrifuged at 10,000 rpm for 5 min and cell free supernatant removed for analysis. Cytokine concentrations (tracheal aspirate and plasma) are simultaneously determined using fluorescent latex beads linked to monoclonal antibodies (R&D Systems, Abington, UK) marked after incubation and coupling with a second phycoerythrin monoclonal antibody (sandwich technique) (R&D Systems, Abington, UK). Final measurement and analysis is done on a Cytomics™ FC 500 Series analyzer (Beckman Coulter Inc., Fullerton, CA, USA).

### Objectives and hypotheses

Our objectives are to achieve a clinically relevant reduction in overall antibiotic use and to reduce treatment costs caused by delayed diagnosis of nosocomial infection. In this study we will test the hypothesis that routine surveillance by determination of cytokine levels in plasma and tracheal aspirates will allow safe discontinuation of antibiotic therapy within 24 hours if the proposed laboratory prediction model indicates absence of infection. We regard a reduction in antibiotic exposure by 15% to be a clinically relevant effect. The second hypothesis we will test is whether early diagnosis reduces the morbidity and costs associated with hospital acquired infection. Ascertaining relevant indicators of morbidity and costs in all patients with culture proven bloodstream infection will operationalize this.

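### The first hypothesis promises safe discontinuation, but no stated null, outcome, margin or sample size addresses harm from stopping antibiotics early

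*Protocol article*

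**What the plan says.** Under Objectives and hypotheses, the first hypothesis to be tested is that surveillance "will allow safe discontinuation of antibiotic therapy within 24 hours if the proposed laboratory prediction model indicates absence of infection". The second is directional: "The second hypothesis we will test is whether early diagnosis reduces the morbidity and costs associated with hospital acquired infection". That section says the second hypothesis is made operational through indicators of morbidity and cost in patients with culture-proven bloodstream infection.

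The Introduction gives two nulls. The primary one reads "The null hypothesis states that the management arms will not differ with respect to antibiotic utilization rate". The other reads "The secondary null hypothesis states that the arms will not differ with respect to costs associated with hospital acquired septic shock".

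Under Measures of outcome, the primary outcome is the rate of systemic antibiotic use. The secondary outcomes are ventilator-free days, inotrope-free days, costs of specific expensive medications and nurse allocation, taken "for all episodes of hospital acquired infection with positive blood cultures for the first 7 days following initiation of antibiotics".

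On deaths, Data collection says "We will collect data on mortality, but this will not be included as a study outcome because of low mortality rates", and it adds the intended study size as a reason.

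The section on sample size sets 2300 days per arm for a 10% reduction in antibiotic use, raised to 3000. Its three further analyses are one of antibiotic prescription prevalence and two of antibiotic-free days.

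**The concern.** Calling discontinuation safe is a claim that patients do no worse. To support it, a trial needs an outcome that would register harm in the patients concerned, and a bound on how much harm is tolerable. The article puts the claim inside a hypothesis it says it will test, and supplies neither.

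At stake is the wording of the conclusion. If antibiotic days fall and the morbidity comparisons are unremarkable, the first hypothesis invites a report that it was confirmed, safety included. Clinicians caring for critically ill newborns and children would act on that word, and the design would not have shown it.

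**Working it through.** **1. What each stated element can show**

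| Element (section) | What it concerns | Bears on harm from early stopping? |
|---|---|---|
| Primary null (Introduction) | Antibiotic utilization, no difference | No |
| Secondary null (Introduction) | Costs of hospital acquired septic shock, no difference | No; a cost null without a margin |
| Primary outcome (Measures of outcome) | Antibiotic days per 1000 days | No |
| Secondary outcomes (Measures of outcome) | Morbidity, cost and nursing in culture-positive hospital acquired episodes | Indirectly, and only in that subset |
| Sample size and three further analyses | Antibiotic use and antibiotic-free days | No |
| Mortality (Data collection) | Recorded, not an outcome | Not tested |

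The population matters as much as the missing margin. The hypothesis is about patients in whom the model indicates no infection. The morbidity outcomes are counted only where a blood culture is positive. A patient whose treatment is stopped early and who deteriorates without a positive culture does not enter them.

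**2. The plan's own sample size**

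Inputs: "in the ICU antibiotic therapy is employed in 40% of patients", a 10% relative reduction (0.40 to 0.36), type I error 5%, power 80%. With pooled p = 0.38,

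n = [1.96 × √(2 × 0.38 × 0.62) + 0.8416 × √(0.40 × 0.60 + 0.36 × 0.64)]² / 0.04² = 2311 per arm, two-sided.

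The stated 2300 is reproduced, with power 0.798 at 2300. So the only sizing in the article is for antibiotic use, and it is sound on those inputs.

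**3. How well harm might be seen (illustrative)**

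The article gives no rate of culture-positive hospital acquired episodes, no outcome SD and no size of harm. Assume a 0.5-SD worsening, independent episodes split evenly between arms, and an unadjusted two-sided 5% t-test. With n episodes per arm, the test has 2n − 2 degrees of freedom and noncentrality 0.5 × √(n/2). The miss rate is 1 − power.

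| Days per arm | Assumed episodes per 1000 days | n per arm | Miss rate |
|---|---|---|---|
| 3000 (stated accrual) | 5 | 15 | 74% |
| 3000 | 10 | 30 | 52% |
| 3000 | 15 | 45 | 35% |
| 3000 | 20 | 60 | 22% |
| 5500 (all 24 months: 2 × 5500 / 2) | 5 | 27.5 | 56% |
| 5500 | 10 | 55 | 26% |

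Power of 80% needs 64 episodes per arm. That is 64/3.0 = 21.3 per 1000 days at 3000 days per arm, or 64/5.5 = 11.6 at 5500. Taking 950 as the midpoint of the stated 900 to 1000 annual admissions, 3000 days correspond to 3000/5500 × 950 = 518 admissions, and 64/518 is about 12% of them.

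At 30 episodes per arm, the 95% confidence half-width is 2.002 × √(2/30) = 0.52 SD. With equal observed means, a 0.5-SD worsening would still not be excluded.

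**The case against.** The strongest reply is that the faulty inference is not in the article. Nowhere does it say that a non-significant morbidity result will be read as safety. The opening objectives, the nulls, the Discussion and the Key messages promise conclusions only on antibiotic use and on costs or morbidity. The safety claim is one adjective in a condensed article, and a harm bound may sit in the full protocol or analysis plan. This stands in part. A reader might infer that safety would be concluded solely from a non-significant test, but the article states no such decision rule, and morbidity could come out significantly better. It does not remove the point. The article itself prints the hypotheses, the nulls, the outcomes and the sizing basis, and on safety they do not match.

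Second, it would be wrong to fault the morbidity outcomes for lacking a margin. They belong to the second hypothesis, which expects improvement, and a null of no difference suits that. This is correct. It also confirms that nothing is left to carry the safety part of the first hypothesis.

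Third, safety information is wider than bloodstream infection episodes. Clinical data are recorded for both groups from the day before culture through the following 6 days, deaths are collected, and antibiotic-free days after any work-up would partly reflect restarted treatment. This too is correct, but none of it is named as a harm outcome or given a criterion.

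Fourth, a reader might infer that there will be too few episodes to see harm, or that harm would usually be missed. The documents do not support either as fact. No episode rate is given, and only three of the six scenarios above have a miss rate over 50%. The planned adjustment for confounders could improve precision, while correlation within patients would worsen it.

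**Conclusion.** The point holds as a mismatch between what the first hypothesis claims and what the stated design can show. This rests on the text alone and does not depend on the number of episodes. Fewer antibiotic days, with or without unremarkable morbidity P values, would not establish that early discontinuation is safe.

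That harm would be poorly estimated is plausible but conditional. It depends on the assumed rate of 5 to 20 episodes per 1000 days, the 0.5-SD effect and the simple t-test. Across that range at the stated accrual, the miss rate runs from 74% down to 22%, so the figures show possible imprecision, not a demonstrated shortfall. The correction should be made because it is cheap and changes what the trial may conclude.

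**What to change.** Delete the word 'safe' from the first hypothesis under Objectives and hypotheses, and limit that hypothesis's confirmatory claim to reduced antibiotic use. Report the morbidity outcomes and the deaths already collected by arm, each with a confidence interval. State that a non-significant difference is not evidence of safety.

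If the sponsor wishes to keep the word, tie it to a harm outcome taken from data already collected in all worked-up patients by arm, as described under Data collection. A margin on ventilator-free and inotrope-free days in culture-positive episodes alone would not test the stated hypothesis. Conclude safety only if the harm-side 95% confidence limit excludes a margin that has been justified and fixed before any comparison of outcomes by arm. If the limit does not exclude it, report the interval and say that safety is not established.

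The first option costs a change of wording and some confidence intervals, with no new patients or data. The second also needs a defined outcome, a reasoned margin and a statement of expected precision. Under either option, the trial may not be able to claim that early stopping is safe.
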